# Effect of auricular electroacupuncture combined with body acupuncture in improving the consciousness of patients after traumatic brain injury

**DOI:** 10.1097/MD.0000000000016587

**Published:** 2019-07-26

**Keywords:** auricular acupoint, body acupuncture, consciousness, electro-acupuncture, GCS, mismatch negativity, traumatic brain injury

## Abstract

**Background::**

Traumatic brain injury (TBI) has become a major cause of morbidity and mortality both in China and abroad. Disorders of consciousness following severe TBI is a common refractory complication, resulting in difficult rehabilitation and poor life quality. However, effective therapeutic approaches remain limited. Although acupuncture has been widely applied in the treatment of neurological disorders in China, its efficacy and safety for consciousness recovery remain to be elucidated.

**Methods::**

Here, we conduct a study design and protocol of a randomized, blinded, controlled study to evaluate the efficacy and safety of electroacupuncture at auricular acupoints “heart” and “brainstem” combined with body acupuncture in the consciousness recovery of patients with TBI. A total of 80 patients with initial Glasgow coma scale score between 3 and 8 points will be recruited in the trial and randomized into intervention (combined application of auricular electroacupuncture and body acupuncture) group or control (conventional treatment) group. Patients in the intervention group will receive electroacupuncture at bilateral auricular acupoints “heart” and “brainstem” (4 points in total) combined with body acupuncture in addition to conventional treatment while patients in the control group will receive conventional treatment alone for 8 weeks. The primary outcomes are changes of Glasgow coma scale score and mismatch negativity of event-related brain potentials at baseline after 4 weeks after the final treatment and 4 weeks after the final treatment. The secondary outcome measures will be changes of Barthel and FuglMeyer scores at baseline after 4 weeks after the final treatment and 4 weeks after the final treatment. The safety will also be assessed by monitoring the incidence of adverse events and changes in vital signs during the study.

**Discussion::**

Results from this trial will significantly support the application of auricular acupuncture and body acupuncture in the consciousness recovery of patients with severe TBI. If found to be effective and safe, auricular acupuncture combined with body acupuncture will be a valuable complementary option for comatose patients with TBI.

**Trial registration::**

Chinese Clinical Trial Registry: ChiCTR1800020245. Registered on 21 December 2018.

## Introduction

1

Traumatic brain injury (TBI) is a leading cause of morbidity and mortality among children and young adults.^[1]^ In China, it is reported that the mortality rate induced by TBI was among 2.7% to 21.8%.^[2]^ Although the number of patients survived from severe TBI increased gradually accompanied by the advance in neurocritical care, many survivors still failed to fully recover a state of disorders of consciousness (DOC) such as coma, vegetative state, and minimally conscious state.^[3]^ The neuropathology of DOC has been extensively described at postmortem and diffuse disruption of subcortical white matter was reported the most common reasons found in victims of TBI induced DOC.^[4,5]^ Longer time to recovery from DOC is predictive of worse prognosis after TBI,^[6,7]^ and shortening the period of DOC may be helpful in improving outcomes, at least partly increase participation in rehabilitation treatment.^[8,9]^ However, only few limited strategies have been found for the treatment of DOC.

As a complementary and alternative therapy, acupuncture is an important component of traditional Chinese medicine and has been widely used in various diseases during the past thousands of years in China. Many types are involved in acupuncture treatment, such as body acupuncture, auricular acupuncture, scalp acupuncture, wrist-ankle acupuncture, and so on. Body acupuncture has been proved in improving consciousness induced by TBI in many studies.^[10,11]^ Auricular acupuncture has also been accepted in many disorders or conditions, such as pain,^[12]^ constipation,^[13]^ addiction,^[14]^ insomnia,^[15]^ cognitive impairment, and dementia^[16]^; however, there combined effect for DOC has not been examined.

Thus, we present a study design and protocol of a randomized, blinded, controlled study to assess the efficacy and safety of auricular electroacupuncture combined with body acupuncture in improving the consciousness in patients with TBI. The objective of this study was to determine if auricular electroacupuncture combined with body acupuncture is more effective than conventional treatment. The results of this study are expected to establish an optimal acupuncture procedure for DOC.

## Methods

2

### Objective

2.1

In this study, the efficacy of combined application of auricular and body acupuncture for consciousness recovery of patients with TBI versus conventional treatment will be evaluated.

### Trial design and setting

2.2

This study is a single-center, randomized controlled, assessor-blinded clinical trial which was devised following the consolidated standards of reporting trials Statement recommendations.^[17]^ The total study period for this trial is 12 weeks (Fig. 1), including 8-week treatment phase and 4-week follow-up phase.

**Figure 1 F1:**
[figure not shown]
Schedule of enrollment, interventions, and assessments.

It will be performed in the GuangDong Second Hospital of Traditional Chinese Medicine. 80 patients who meet the eligibility criteria and sign an informed consent form will be randomly divided into 2 groups to receive either auricular electroacupuncture plus body acupuncture or conventional treatment in a 1:1 ratio. Acupuncture will be performed 30 minutes per day, 5 days per week for 8 weeks. Doctors with more than 5 years of clinical experience will be allowed to perform the interventions. The flowchart of the trial is shown in Figure 2.

**Figure 2 F2:**
[figure not shown]
Flow chart of the study procedure.

### Participants

2.3

#### Recruitment strategies

2.3.1

Inpatients at acupuncture departments in GuangDong Second Hospital of Traditional Chinese Medicine will be recruited mainly in this randomized controlled trials. Additionally, posters will be put in the hospitals and a Chinese multipurpose social media named WeChat will be applied to recruit. Brief descriptions of eligible criteria, the free acupuncture treatments and the possible risks of the trial will be marked and all patients’ family members have the right to participate or drop out at any time, and will be required to sign the informed consent before the trial begin.

#### Eligibility criteria: inclusion criteria

2.3.2

The inclusion criteria will be as follows.

1.Meet the diagnostic criteria for TBI;2.Aged 18 to 70 years old, male or female;3.Initial GCS score between 3 and 8 points on admission and lasted more than 2 weeks;4.Imaging (magnetic resonance imaging) head has no obvious shift, missing, large necrosis of brain structure change and obvious brain stem (not including pyramidal tract) or thalamic lesions, each lobe lesions range can not exceed 30% of the scope of 1 side of the brain;5.No primary consciousness disorder and limb functional activity disorder;6.Signed informed consent.

#### Eligibility criteria: exclusion criteria

2.3.3

The exclusion criteria will be as follows.

1.DOC not induced by TBI;2.Clinical course more than 1 year;3.Combination of heart, liver or kidney failure endanger the safety of life at any time;4.Younger than 18 years or older than 70 years;5.Those who do not receive electroacupuncture therapy;6.Women with pregnancy and lactation.

### Randomization and allocation

2.4

Random numbers will be generated by the random number generator in the SPSS statistical software package (version 20.0, IBM SPSS Statistics, IBM Corp, Somers, NY). Another specified researcher who is not involved in the study was responsible for it.

The allocation of participants will be sealed in a sequentially numbered opaque envelope. If the participant meets the inclusion criteria and signs informed consent, the above-specified researcher will sequentially give the sealed random number envelope to the physician, who will open the envelope and allocate the participant to either intervention group or control group according to the random number.

### Blinding

2.5

Because of the add-on study design, a single-blinded method will be used. While the participants and practitioners cannot be blinded, we blinded the outcome assessors, data manager, and statistics analyzer. The assessor will be instructed not to communicate with participants about the possibility of their treatment. James et al's blinding index will be evaluated after the completion of the study to evaluate the success of blinding.^[18]^

### Intervention

2.6

In the 8-week treatment phase, participants in both groups will receive conventional treatment, and those allocated to the intervention group will also receive auricular electroacupuncture combined with body acupuncture treatment.

### Conventional treatment in both groups

2.7

All the participants will accept conventional treatment, including the prescription of coma arousal and neuroprotective medicines. Details of conventional treatment used during the trial will be recorded, noting any change and the reasons.

Auricular electroacupuncture combined with body acupuncture in the intervention group.

In addition to conventional treatment, patients in the intervention group will receive both auricular point electroacupuncture and body acpuncture. Auricular point electroacupuncture manipulation was as follows: Following disinfection of skin with 75% alcohol, bilateral auricular acupoints “heart” and “brainstem”^[19]^ (4 points in total) will be stimulated using disposable and stainless needles (13 mm long and 0.25 mm in diameter, Suzhou Huanqiu Acupuncture Medical Appliance, Suzhou, China) inserted to a depth of 2 mm, and connected to an electrical stimulator (SDZ-V EA; Huatuo, Suzhou, China) with a frequency of 2/10 Hz and current of 1 mA. Body acupuncture manipulation was as follows: After disinfection, GV26^[20]^ was inserted towards the nose at a depth of 10 mm while bilateral PC6^[20]^ and SP6^[20]^ was perpendicularly inserted at a depth of 20 mm by disposable and stainless needles (40 mm long and 0.30 mm in diameter, Suzhou Huanqiu Acupuncture Medical Appliance). The needle will be manipulated using twirling, lifting, thrusting, and mild reinforcing-reducing methods to promote Qi. Eye moisture or the presence of tears will be used as an indicator of Qi arrival since patients are not able to express their feelings. Acupuncture will be restrained for 30 minutes, once daily, 5 times a week and lasted for 8 weeks. The location of acupoints applied was shown in Table 1.

**Table 1 T1:**
[figure not shown]
Description of the applied auricular points.

### Discontinuing interventions

2.8

The trial will be ceased if one of the following conditions appeared:

(1)a serious poststroke complication arises; or(2)recurrent stroke or any other severe condition occurs leaving the patient in a critical condition.

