### Safety assessment

2.10

Any adverse events, including acupoint hematoma, infection, dizziness, and apostasies will be evaluated during the whole treatment by the researcher. If any severe adverse events occurring, acupuncture intervention will be ceased immediately and the principal investigator will be informed to take proper actions. 1 month will be followed up after the trial in case of subsequent adverse events.

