### Sample size calculation

2.12

The trial is designed to determine the role of auricular and body acupuncture in the consciousness recovery of patients with TBI and prove that auricular and body acupuncture is superior to conventional treatment. Therefore, GCS change will be used as an evaluation index. According to our previous pilot study, the change of GCS before and after treatment in the intervention group was shown to be 5.62 ± 1.41 (n = 8) and that in control group was 4.50 ± 1.85 (n = 8). Sample size was estimated using the following formula: 

where n represents the number of samples required, n = n_1_ + n_2_, *Q*_1_ = n_1_/n, Q_2_ = n_2_/n with a significance level (*α* = 0.05) of a 2-sided 2-sample *t* test and 80% power to detect a difference between the 2 groups. Thus, a total sample size of 80 patients will be recruited allowing for 10% of attrition, with 40 in each.

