### Statistical analysis

2.13

SPSS 20.0 (IBM SPSS Statistics, IBM Corp, Somers, NY) will be used to analyze the data. Quantitative data will be presented as mean ± standard deviation. GCS Barthel and FuglMeyer scores will be conducted between the 2 groups by a superiority independent sample *t* test with a 95% confidence interval. The incidence of complications and adverse events will be compared by *χ*^2^ test. A mixed model procedure will be applied to compare longitudinal changes in MMN amplitude between the 2 groups. Any missing data will be replaced by the last measured value. For all analyses, *P* values of less than .05 will be considered statistically significant.

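### Section 2.8 is wrong as written: its named triggers presuppose a stroke in a TBI trial, and it stops the trial where its heading, its single-patient trigger and section 2.10 point to stopping treatment (minor)

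*Protocol article*

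**What the plan says.** All references are to the protocol article.

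- **Section 2.8 (Discontinuing interventions).** The action is "The trial will be ceased if one of the following conditions appeared". Two conditions follow: first, "a serious poststroke complication arises"; second, "recurrent stroke or any other severe condition occurs leaving the patient in a critical condition".
- **Sections 2.3.2 and 2.3.3 (eligibility).** Patients must meet the diagnostic criteria for TBI, and a disorder of consciousness from any other cause is an exclusion. No criterion mentions stroke.
- **Section 2.10 (Safety assessment).** "If any severe adverse events occurring, acupuncture intervention will be ceased immediately", and the principal investigator is informed.
- **Section 2.6 (Intervention).** Both arms receive conventional treatment, and "those allocated to the intervention group will also receive auricular electroacupuncture combined with body acupuncture treatment". Control patients therefore have no acupuncture to stop.
- **Sections 2.12 and 2.14.** The sample size allows for 10% attrition, and individual dropouts and withdrawals are to be recorded.
- **Section 2.13 (Statistical analysis).** "Any missing data will be replaced by the last measured value".

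**The concern.** Section 2.8 is an operative rule that staff at the site would have to apply, and it has two faults.

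**Triggers.** A post-stroke complication and a recurrent stroke both presuppose a stroke that is no part of this trial's entry condition. Only the general limb of the second trigger, any other severe condition, fits the enrolled patients without qualification.

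**Action.** The heading speaks of interventions and the second trigger of one patient's state, yet the sentence stops the trial. Section 2.10 attaches a narrower action to overlapping events, and nothing says which section governs.

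The text leaves three possible actions: stop the trial, end the patient's participation, or stop that patient's acupuncture. The choice matters for the data, because the second action removes later outcome values and the third does not. Patients enter with a GCS of 3 to 8 that has lasted more than two weeks, so a critical event during 12 weeks is foreseeable.

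**Working it through.** Section 2.8 contains no figure to reproduce. The check compares the texts and then sizes the one analytic consequence.

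**1. Triggers against population.** Entry requires TBI, and other causes of the disorder of consciousness are excluded. A TBI patient may have had a stroke before, since prior stroke is not itself an exclusion. The stroke triggers are therefore ill-chosen rather than impossible; the post-stroke complication, listed first, is the clearer error.

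**2. Action against the rest of the article.**

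| Place | What it implies |
|---|---|
| 2.8, text | the trial stops |
| 2.8, heading | an intervention stops |
| 2.8, second trigger | the event concerns one patient |
| 2.10 | acupuncture stops, principal investigator informed |
| 2.12 and 2.14 | attrition and single withdrawals are expected, so the trial goes on |

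Only the operative sentence points to the whole trial.

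**3. The literal reading.** If each of 80 patients independently has probability p of a qualifying event, the chance of at least one is 1 − (1 − p)^80. The article gives no p. Assumed values of 0.5%, 1%, 2% and 5% give 33%, 55%, 80% and 98%. This shows how easily the printed rule would be met. It is not a forecast that the trial will stop.

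**4. The reading in which participation ends.** Inputs from section 2.12: 40 patients per arm, and pilot GCS changes of which "the intervention group was shown to be 5.62 ± 1.41" and "that in control group was 4.50 ± 1.85". The pilot difference is 5.62 − 4.50 = 1.12.

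Suppose a patient loses d GCS points between the last assessment and a missed one, and the last value is carried forward.

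- Overstatement of that arm's mean change: d/40.
- For d = 1 (assumed): 1/40 = 0.025.
- Relative to the pilot difference: 0.025/1.12 = 2.2%.

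In the intervention arm this inflates the estimated effect; in the control arm it shrinks it. Equal losses in one patient of each arm cancel.

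**5. The reading in which only treatment stops.** Outcome assessments continue, nothing is carried forward because of section 2.8, and the shift is zero.

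**The case against.** The best defence is that section 2.8 should be read under its heading. It then stops the intervention for the patient concerned, agrees with section 2.10, and has nothing to stop in a control patient. Sections 2.12 and 2.14 support this, since a trial that ended with its first critical patient would not need to plan for attrition. Last-value replacement is also a feature of section 2.13 that affects any dropout, and rewording section 2.8 leaves it in place.

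Much of this stands. Patient-level stopping was probably meant, and the carry-forward problem comes from section 2.13. The defence still requires the reader to set aside the operative sentence in favour of the heading, and it does not explain the stroke triggers.

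Four stronger conclusions might be inferred, and the article supports none of them.

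- **The sickest patients leave the trial.** This is one reading only. No section says that outcome visits end once section 2.8 applies.
- **One patient could shift the result by 10% or more.** Losing a whole pilot mean gain would give 4.50/40 = 0.1125 (10.0% of 1.12) in control or 5.62/40 = 0.1405 (12.5%) in the intervention arm. Those gains are changes from before to after treatment. The patient would have to have recorded the full gain at an assessment before the missed one and then lost all of it, which the article does not show.
- **TBI patients are left unprotected.** The general limb of the second trigger and section 2.10 cover critical events after TBI.
- **The sample size is affected.** Nothing in section 2.8 enters that calculation.

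**Conclusion.** The point holds as an error in the text of section 2.8. Its two named triggers belong to a stroke population, and its stated action contradicts its heading, its single-patient trigger, section 2.10, and the attrition and withdrawals planned for in sections 2.12 and 2.14. This is a complete sentence that states the wrong thing, not detail left to a fuller document.

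The analytic consequence is conditional and small. It arises only if participation ends and the last GCS value predates the deterioration. It is then d/40 per patient, 0.025 or about 2% of the pilot difference for an assumed loss of one point. It would become material only with several such events, unevenly split between the arms, and no event rate is available to judge that. Severity: minor.

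**What to change.** Reword section 2.8 in three steps.

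1. Delete both stroke triggers. Keep the general one: any severe condition that leaves the patient critically ill. The investigators may add events relevant to TBI.
2. Replace the action with: *acupuncture will be stopped for that patient*. This brings it into line with section 2.10.
3. Add: *patients in either arm remain in the scheduled outcome assessments where feasible*. For a control patient, only this sentence has any effect.

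The cost is an amendment to one section, sent to the ethics committee by the route that section 2.15 already provides. The one practical burden is that assessments already on the schedule are kept for a few critically ill patients, hence the words on feasibility. No new visits, procedures or patients are needed. The change does not alter the last-value rule in section 2.13, which would still apply to values missing for other reasons.

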### Outcome measures

2.9

The primary efficacy endpoint will be the Glasgow Coma scale (GCS) and mismatch negativity (MMN) at baseline after 4 weeks after the final treatment and 4 weeks after the final treatment. The secondary outcome measures will be changes of Barthel and FuglMeyer scores at baseline after 4 weeks after the final treatment and 4 weeks after the final treatment. Safety will be assessed by monitoring adverse events as well as changes in vital signs during the study.

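### GCS and MMN are both primary with no success rule and no primary visit, every test is judged at unadjusted P<.05, and the trial is sized on GCS change alone

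*Protocol article*

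**What the plan says.** Section 2.9 (Outcome measures) states: "The primary efficacy endpoint will be the Glasgow Coma scale (GCS) and mismatch negativity (MMN". The Abstract (Methods) uses the plural: "The primary outcomes are changes of Glasgow coma scale score and mismatch negativity of event-related brain potentials". Neither place ranks the two measures or says whether one or both must show a difference.

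The timing in section 2.9 reads "at baseline after 4 weeks after the final treatment and 4 weeks after the final treatment". The wording is garbled. Baseline and at least one later assessment are certain and two or more later ones are likely, but no visit is named as primary.

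Section 2.13 (Statistical analysis) assigns the tests. For GCS: "GCS Barthel and FuglMeyer scores will be conducted between the 2 groups by a superiority independent sample" t test, with no visit given. For MMN: "A mixed model procedure will be applied to compare longitudinal changes in MMN amplitude between the 2 groups". For all analyses, P "values of less than .05 will be considered statistically significant".

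Section 2.12 (Sample size calculation) uses GCS only: "Therefore, GCS change will be used as an evaluation index". It takes a 2-sided alpha of 0.05, 80% power and 10% attrition, and arrives at 40 patients per arm. MMN has no part in it.

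**The concern.** Sections 2.9, 2.12 and 2.13 do not describe the same trial. The error rate and power in section 2.12 belong to one test of GCS change, done once. Section 2.9 sets up at least two primary tests, and section 2.13 lets each be called significant at .05.

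Either way of resolving this has a cost. If either measure can win, the chance of a false claim exceeds 5%. If both must win, the error is controlled, but the 80% power has been worked out for GCS only.

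As written, a result on MMN alone, or on GCS at one favourable visit, could be presented as proof of efficacy, and the choice could be made after the results are seen. The trial is meant to demonstrate superiority (section 2.12), so its main conclusion is at stake.

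**Working it through.** **1. Reproduce the plan's sample size.** Inputs from section 2.12: GCS changes of 5.62 (SD 1.41) and 4.50 (SD 1.85).
- Difference: 5.62 − 4.50 = 1.12.
- Pooled SD: √[(1.41² + 1.85²)/2] = 1.645.
- Standardised effect: 1.12/1.645 = 0.681.
- A 2-sided t test at .05 with 80% power needs 35 per arm. Then 35/0.9 = 38.9, so 39 per arm or 78 in total. The stated 80 is confirmed to within rounding, for one GCS test.
- Evaluable after attrition: 40 × 0.9 = 36 per arm. Power for GCS at .05 is then 81.3%.

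**2. Type I error if any one primary test counts as success.** The documents give no correlations, so those below are assumptions applied to the test statistics. The correlated cases come from simulating 2-sided normal tests.

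| Primary tests | Correlations assumed | Overall error |
|---|---|---|
| 1 GCS + 1 MMN model | independent: 1 − 0.95² | 9.75% |
| 1 GCS + 1 MMN model | GCS-MMN 0.5 | 9.1% |
| 2 GCS visits + 1 MMN model | GCS visits 0.7, GCS-MMN 0 | 12.9% |
| 2 GCS visits + 1 MMN model | GCS visits 0.7, GCS-MMN 0.5 | 11.9% |
| 2 GCS visits + 1 MMN model | GCS visits 0.5 to 0.9, GCS-MMN 0 to 0.5 | 10.8% to 13.7% |

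MMN is counted once because section 2.13 gives it one longitudinal model. Extra visits therefore add tests mainly for GCS.

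**3. If both must succeed at one fixed visit.**
- Error: at most 5%, because a false claim needs at least one true null hypothesis to be rejected at .05.
- Power: no greater than the power for GCS, 81.3%. If MMN had 80% power and were independent of GCS, joint power would be 0.813 × 0.80 = 65%. The documents give no MMN effect size, so this is an illustration only.

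**4. If either suffices and alpha is controlled.**
- At .025 (Bonferroni), GCS power with 36 evaluable per arm is 72.4% by the t test.
- Under Holm, GCS is tested at .05 once MMN has passed .025, so 72.4% is the floor for GCS power. If MMN independently had the same 72.4% power at .025, GCS power would be 0.724 + 0.724 × (0.813 − 0.724) = 79%.
- Keeping 80% power for GCS at .025 would take 43 evaluable per arm by the t test. Then 43/0.9 = 47.8, so 48 per arm or 96 in total.

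**The case against.** The strongest reply is that no inflation has been shown. Section 2.9 joins the two measures with a conjunction under a singular noun, which can be read as requiring both. At one fixed visit that keeps the error at 5% or less. This stands as far as the number goes: without a success rule the overall rate is undefined, and every inflated figure is conditional. It does not remove the defect, because the plural in the Abstract and the blanket .05 in section 2.13 leave the other reading equally open. The both-required reading also leaves power unsupported for MMN.

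A reader might infer that the false-positive rate simply is 10-16%. The documents do not support that. It presumes that any single result suffices, and its upper end needs two MMN tests where section 2.13 specifies one model. A reader might also infer that requiring both certainly loses the 80% power. That cannot be shown either: with very high MMN power, joint power could approach 81%.

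A second reply is that a multiplicity rule usually sits in the statistical analysis plan and that an article condenses the protocol. That would answer mere silence. Here the article itself fixes two primaries and one unadjusted threshold for everything, so an analysis plan that added an adjustment would contradict it.

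A third reply is that section 2.12 already makes GCS the real primary. It does not: "GCS change will be used as an evaluation index" serves the sizing, names no visit and does not demote MMN.

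**Conclusion.** The point holds, with its size conditional on a rule that the plan does not state. Two measures are primary, no visit is primary, and each analysis may be declared positive at .05, while the sample size covers GCS change alone.

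- Any one result suffices: overall error about 9-10% with one GCS test and one MMN model, about 12-13% with two GCS visits. The second figure rests on an assumed correlation of 0.7 between GCS visits and 0 to 0.5 between GCS and MMN.
- Both required at one fixed visit: error at or below 5%, joint power capped at about 81%. The 65% figure rests on assumed, independent 80% power for MMN.

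Confidence is high that the rule must be fixed before analysis. It is lower for any single error rate, since the documents settle neither the number of GCS tests nor the correlations.

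**What to change.** In sections 2.9 and 2.13, name GCS change from baseline at one stated visit as the sole primary endpoint, which agrees with the sizing in section 2.12. The end of the 8-week treatment phase is a candidate if the pilot change in section 2.12 was measured then; the authors need to confirm this. Test one prespecified contrast from the MMN mixed model at .05 only if GCS is significant. Report the other visits and scales as secondary, without confirmatory claims. This keeps alpha at .05, the GCS power and the 80 patients.

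The costs are that MMN alone can no longer carry the trial, and that the change is a protocol amendment needing ethics committee approval (section 2.15) while recruitment is under way (section 3.1). It should be made without sight of outcome data by arm.

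Other rules are valid if the authors prefer to keep both measures primary:
- Either suffices: use Holm, and state that GCS power at 36 evaluable per arm is at least about 72% rather than 80%.
- Both required: say so, fix the visit, and justify power for MMN with a stated effect size.
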